#### 2.3.6. Phase 6: Comprehensive Gnathological Assessment

A comprehensive gnathological assessment will be performed to obtain a multidimensional profile of the participant’s craniofacial and mandibular health, integrating both clinical and behavioral dimensions. This process begins with a structured clinical questionnaire designed to collect detailed information on medical history, previous traumas, dental and medical treatments, systemic conditions, and current symptoms. It further investigates habits and parafunctional behaviors, including bruxism, nail-biting, gum chewing, tongue pressure, and the use of visual orthopedic devices. Additionally, sleep quality, occupational posture, and potential associations between stress and symptom onset are explored. Physical features, pain, and functional limitations will be evaluated through Axis I, while psychosocial factors, emotional status, and behavioral patterns will be studied using Axis II.

Muscular function during static and masticatory activities will be studied with a 4-channel surface electromyographic examination (Teethan) [59].

Ascending or descending interference factors in temporomandibular disorders will be identified through the cervical ROM tests, balance tests, and walking tests, using the Baiobit [60,61].

#### 2.3.7. Follow-Up Assessment

During this phase, we provided some process variables, as follows, to evaluate the feasibility, fidelity, and overall quality of the study’s execution.

Protocol Adherence. The extent to which participants and investigators followed the study’s predefined procedures, including eligibility, intervention delivery, and assessment schedules.

Completion of Questionnaires. The percentage of participants who fully completed all self-reported outcome measures at each designated time point in the study.

Patient Participation. The engagement level of participants in study activities, including attendance, assessments, and cooperation.

Dropouts. The number of participants who left the study early, with reasons such as personal choice, adverse events, loss to follow-up, or investigator decision.

Adverse Events. Any unintended harmful occurrences experienced by participants during the study were evaluated for frequency, severity, and connection to the study intervention.

Adherence to Study Timelines. The degree to which recruitment, intervention delivery, and data collection adhered to planned schedules.

We also intend to conduct telephone outreach to participants who choose to withdraw from the study.

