#### 2.2.4. Phase 4: The Follow-Up

All evaluations will be re-executed after six (T1) and twelve (T2) months from the start of the study. During follow-up appointments, we will update specific process variables, described below.

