### 2.4. Statistical Analysis

The primary efficacy analysis will be performed in the intention-to-treat (ITT) population. The pre-protocol population consisted of all patients in the ITT population without major protocol deviations and will be used for the supportive analysis of the primary efficacy endpoint.

The quantitative data collected, organized into two distinct groups of subjects, will be presented in tables that include the mean and standard deviation. In addition, qualitative data will be represented through frequency distributions.

The primary endpoint (number of MIGs/month from baseline to 6 and 12 months) will be analyzed using a linear mixed-effect model (LMEM) with treatment group × time as the fixed effect and the baseline number of MIG/month value as the covariate.

For qualitative data analysis, the Chi-square test will be implemented.

The scores obtained from the evaluation scales will be correlated with the clinical parameters of the participants, when applicable, using the Pearson or Spearman correlation coefficients, contingent upon the distribution of the data.

In the case of individuals with MIG, a logistic regression analysis will be performed to investigate potential associations between psychopathological parameters and the response to headache treatment. Adherence to both PA and TPE will be incorporated as process variables in the analyses. Dietary adherence scores from the Mediterranean Diet Assessment Tool, Diet Risk Score, and food-headache diaries will be assessed longitudinally for their potential as predictors of migraine outcomes. Additionally, EXE adherence will be evaluated through attendance records and wearable device data.

Analyses will be limited to participants with complete data on different measurements. We hypothesized that missing data occur randomly into two group. We plan to gather additional information from participants who drop out.

Should the dropout rate exceed our projections, we will employ a regression model to impute the missing data.

The exploratory outcomes will be evaluated utilizing the same LMEM employed for the primary analysis, without adjustments for multiple comparisons. Conclusions will be derived from effect size estimates, specifically Cohen’s d, accompanied by a 95% bootstrap confidence interval (CI). Effect sizes will be systematically classified as small (d = 0.2), medium (d = 0.5), and large (d = 0.8).

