According to recent studies, regular personalized PA [36] has been associated with a reduction in systemic inflammation (maybe linked to modulation of endorphin and serotonin systems), and improvement in sleep and mood. Moreover, scientific evidence shows that physical inactivity [120], poor EH [113], being overweight, and mood or sleep disorders contribute to the chronicity of the disease. Compared to previous experiences [121], this model may contribute to the ongoing development of interdisciplinary strategies for MIG management, incorporating conventional pharmacological therapies with a structured regimen of TPE and supervised EXE, while also including the assessment of EH as a non-differential component across groups [109]. Despite being relatively underexplored in the literature, some TPE experiences are starting to be documented [122,123], but to our knowledge, none of these include nutritional, neurological, posturological, gnathological, and kinesiological assessment plus supervised PA. This aspect is mainly innovative because EXE is considered a trigger by people with MIG, and they tend to avoid it [124], developing kinesiofobia [125]. Moreover, MIG pain limited PA in people who suffered [124]. The proposed model may help guide individuals with MIG toward engaging in PAs within a supervised and individualized setting, customizing the program according to postural and gnathological assessment. In fact, certain temporomandibular disorders and postural alterations can aggravate symptoms, promoting muscle tension and the activation of trigeminal nociceptive circuits [33]. Improving these aspects may contribute to reducing peripheral nociceptive inputs, preventing recurrent activation of the trigeminal-vascular system. Thanks to improved neuromuscular function and neurogenic inflammation, a reduction in allodynia and central sensitization can be expected [67].

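### Contact with leavers is described in two different scopes and never aimed at the monthly migraine count, while a complete-data rule excludes them from the intention-to-treat result

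*Protocol article*

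**What the plan says.** Post-exit contact appears twice in the protocol article. Section 2.3.7 defines dropouts broadly: "The number of participants who left the study early, with reasons such as personal choice, adverse events, loss to follow-up, or investigator decision". The same section then says: "We also intend to conduct telephone outreach to participants who choose to withdraw from the study". Section 2.4 has a wider sentence: "We plan to gather additional information from participants who drop out". Neither sentence says what will be asked or when.

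On scheduled follow-up, Section 2.2.4 says: "All evaluations will be re-executed after six (T1) and twelve (T2) months from the start of the study". It does not make this depend on continuing the exercise programme.

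On analysis, Section 2.4 says: "The primary efficacy analysis will be performed in the intention-to-treat (ITT) population". It also says "Analyses will be limited to participants with complete data on different measurements" and "We hypothesized that missing data occur randomly into two group". Regression imputation is reserved for dropout above what was projected. The only dropout figure in the article is the 30% in the Sample Size paragraph, for 200 participants in total.

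**The concern.** An intention-to-treat estimate needs the outcome from randomised participants whether or not they completed the programme. For people who leave, the planned contact is the only stated means of obtaining that outcome. It is described inconsistently and is not directed at the endpoint. The complete-data rule then removes those without full data, and the imputation provision stays inactive unless dropout passes 30%.

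The result would be an analysis called intention-to-treat that in practice rests on completers. Allowing for dropout in the sample size is meant to protect power. It does nothing about bias if those who leave differ from those who stay, and the article gives reasons in both arms to expect that they do.

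**Working it through.** **1. Scope of contact, side by side.**
- Section 2.3.7, telephone call: voluntary withdrawals only, which is one of the four exit reasons listed there. Content and timing not stated.
- Section 2.4, further information: all who drop out, hence all four reasons. Content and timing not stated.
- The wider sentence does reach people who leave for an adverse event or by investigator decision. What is missing from both is a link to the monthly migraine count at 6 and 12 months.

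**2. How many can be lost before imputation starts.** Inputs are 200 randomised and 30% projected dropout (Sample Size paragraph). Then 0.30 × 200 = 60. Up to about 60 participants can leave with the imputation provision untouched and the complete-data rule in force.

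**3. Interaction with the model.** The primary model is a linear mixed-effects model on the 6- and 12-month counts, with baseline as a covariate. Such a model can use a participant with only one of the two follow-up counts. If complete data means all visits, someone who leaves after 6 months loses a usable count. On the milder reading (complete for the measurement in question), someone who leaves before 6 months still contributes nothing, because baseline enters only as a covariate.

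**4. Is random missingness plausible on the article's own account?**
- Intervention arm: the Discussion states that "EXE is considered a trigger by people with MIG, and they tend to avoid it", and only this arm has an exercise programme.
- Control arm: the Discussion's limitations paragraph foresees demoralisation with more dropout and poorer diary completion among controls.
- Both remarks describe leaving for reasons tied to allocation and symptoms.

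**5. What the bias could be (illustration; the article gives none of these rates).** Let m be the share of an arm that is missing, and g the number of days by which leavers improve less than those observed. Observed minus true mean improvement in that arm is m × g, so

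bias in the treatment difference = m(exercise) × g(exercise) − m(control) × g(control),

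with a positive value favouring exercise.

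| Assumption | Bias (days) |
|---|---|
| Exercise arm only, m = 10%, g = 1 | 0.10 × 1 = +0.1 |
| Exercise arm only, m = 30%, g = 3 | 0.30 × 3 = +0.9 |
| Both arms, m = 30%, g = 2 | 0.6 − 0.6 = 0 |
| Exercise m = 10%, control m = 30%, g = 2 in both | 0.2 − 0.6 = −0.4 |
| Control arm only, m = 30%, g = 3 | 0 − 0.9 = −0.9 |

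The planned difference is nearly 2 days, so 0.1 to 0.9 days is 5% to 45% of it. If control leavers would have done better than those who stay, g(control) is negative and the second term adds to the bias instead of offsetting it.

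**The case against.** The strongest reply is that the two contact sentences are compatible: one names a method for voluntary withdrawals, the other a general aim for all dropouts. Call scripts and timing are also what a condensed article leaves to the full protocol. That is fair, and the absence of operational detail alone would not be a point. What stands is that the article itself fixes the analysis rule: complete data only, with imputation only above the projection. Under that rule, information gathered from leavers has no stated route into the primary result.

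A reader might infer more: that people who stop exercising because of harm or by investigator decision are lost to the endpoint, and that the benefit is therefore overstated. The documents do not support this.
- No section says that stopping exercise ends follow-up. The 6- and 12-month evaluations are unconditional, attendance is tracked separately from dropout, and the 12-week programme is due to end before the first follow-up visit.
- The wider sentence in Section 2.4 covers these exit reasons.
- One can calculate that, if leavers get no benefit, continuers get 2 days and controls do not change, 15% exit would show 2.00 days against a true 0.85 × 2 = 1.70 (18% too large), and 30% exit 2.00 against 0.70 × 2 = 1.40 (43% too large). No exit rate for this route is given, 30% is the figure for all dropout, and possible control-arm dropout is ignored.
- Under-recording of harms does not follow either. Adverse events are recorded both as a dropout reason and in their own right, and exercise sessions are supervised.

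**Conclusion.** The point holds in a limited form. The two statements on contact differ in scope and neither is aimed at the primary count. Together with the complete-data restriction, they leave up to about 60 of 200 participants outside an analysis described as intention-to-treat. This takes the 30% in the Sample Size paragraph to be the projection that Section 2.4 means.

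The random-missingness assumption sits badly with the article's own remarks about both arms. The size and direction of the resulting bias are not known. The range of −0.9 to +0.9 days shows only what plausible inputs could do, and it should not be quoted as an expected overstatement of benefit.

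**What to change.** - Reconcile Sections 2.3.7 and 2.4 so that contact covers every exit reason except refusal of further contact.
- State explicitly that participants who stop the exercise programme remain on the 6- and 12-month schedule already set in Section 2.2.4.
- Use the planned calls to collect the monthly migraine count, current preventive drug and adverse events at 6 and 12 months.
- Enter these counts in the intention-to-treat mixed model, flagged as recall-based so that the analysis can be repeated without them.
- Drop the complete-data restriction for the primary endpoint, so that every available follow-up count is used.

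The cost is amended wording and calls to up to about 60 people at one or two time points, using outreach that is already planned. The downside is that counts recalled by telephone are less precise than the diary counts that the article uses elsewhere. The change should be made before participants begin to leave, because counts not collected during the trial cannot be reliably recovered afterwards.

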### 2.4. Statistical Analysis

The primary efficacy analysis will be performed in the intention-to-treat (ITT) population. The pre-protocol population consisted of all patients in the ITT population without major protocol deviations and will be used for the supportive analysis of the primary efficacy endpoint.

The quantitative data collected, organized into two distinct groups of subjects, will be presented in tables that include the mean and standard deviation. In addition, qualitative data will be represented through frequency distributions.

The primary endpoint (number of MIGs/month from baseline to 6 and 12 months) will be analyzed using a linear mixed-effect model (LMEM) with treatment group × time as the fixed effect and the baseline number of MIG/month value as the covariate.

For qualitative data analysis, the Chi-square test will be implemented.

The scores obtained from the evaluation scales will be correlated with the clinical parameters of the participants, when applicable, using the Pearson or Spearman correlation coefficients, contingent upon the distribution of the data.

In the case of individuals with MIG, a logistic regression analysis will be performed to investigate potential associations between psychopathological parameters and the response to headache treatment. Adherence to both PA and TPE will be incorporated as process variables in the analyses. Dietary adherence scores from the Mediterranean Diet Assessment Tool, Diet Risk Score, and food-headache diaries will be assessed longitudinally for their potential as predictors of migraine outcomes. Additionally, EXE adherence will be evaluated through attendance records and wearable device data.

Analyses will be limited to participants with complete data on different measurements. We hypothesized that missing data occur randomly into two group. We plan to gather additional information from participants who drop out.

Should the dropout rate exceed our projections, we will employ a regression model to impute the missing data.

The exploratory outcomes will be evaluated utilizing the same LMEM employed for the primary analysis, without adjustments for multiple comparisons. Conclusions will be derived from effect size estimates, specifically Cohen’s d, accompanied by a 95% bootstrap confidence interval (CI). Effect sizes will be systematically classified as small (d = 0.2), medium (d = 0.5), and large (d = 0.8).

All statistical analyses will be completed using IBM SPSS^®^ Statistics for Windows version 25.0 (IBM Corp., Armonk, NY, USA).

*Sample Size.* The sample size calculation was based on real-life data regarding the response rate to therapy through PA in people with MIG, specifically focusing on the number of headache days. According to the literature, this approach indicates a decrease of approximately 15–20% relative to baseline data [98]. To determine the number of participants in the intervention and control groups, we referenced various articles on the subject, particularly the work of Krøll et al. [98,99], which indicates that the average difference in the number of headache days is almost 2 days less than the baseline. The standard deviation is estimated to be approximately 50% of the average for both groups. Assuming a 1:1 ratio, with a significance level of 5% and a statistical power of 80%, a sample size of a total of around 200 participants (100 patients per group) will be determined, accounting for an anticipated dropout rate of 30%. The recruitment of this cohort will be scheduled for over 9 months to effectively achieve the desired enrollment.

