### 2.1. Study Design

The EXEMIG/01 study was a rigorously designed, randomized, controlled, non-blinded interventional trial. This study is non-blinded due to the nature of the intervention, which may introduce performance and assessment bias, particularly with regard to self-reported outcomes. To minimize this risk, standardized procedures, validated questionnaires, and objective measures (e.g., wearable accelerometers) will be used wherever possible.

A total of 200 individuals suffering from episodic high-frequency or chronic MIG (diagnosed following the international criteria outlined in the ICHD Classification 2018 [53]) will be invited to participate voluntarily in this project. Participants will be selected from those attending the Headache Center at Santa Maria della Misericordia Hospital in Perugia, following the usual CUP booking procedures for a neurological consultation. The inclusion criteria were as follows: chronic (≥15 attacks/month, for at least 3 months) or episodic and high frequency (8–14 attacks/month) MIG; age range 18–65 years; PA levels lower than WHO recommendations (engage in 150 to 300 min of weekly moderate-intensity aerobic PA, or 75 to 150 min of vigorous-intensity aerobic activity, or a combination of both that is equivalent [54]); and ability to walk independently. The exclusion criteria were as follows: age younger than 18 years or older than 65 years; clinical evidence of serious cardiovascular, central nervous system, or significant musculoskeletal disease that may limit or contraindicate EXE; and failure to provide written consent for participation in the study.

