### 2.2. Project Phases

#### 2.2.1. Phase 1: Enrollment and Medical Assessment

All participants will be invited to attend their first specialist visit to the Headache Center of the Santa Maria della Misericordia Hospital in Perugia. The neurologist conducts a thorough interview covering the onset and evolution of the headache, its frequency, duration, and intensity, associated symptoms (nausea, vomiting, photophobia, phonophobia), presence of aura, triggering and relieving factors, family history, sleep quality, stress levels, and menstrual cycle in women.

During the neurological assessment, we will collect comprehensive information for each participant, including age, sex, age of headache onset (in years), potential onset of MIG chronicity (in years), existing comorbidities, other medications being utilized, and symptomatic medications used as needed (with a focus on their efficacy). Furthermore, we will gather details regarding prophylactic medications (usage timing, dosage, potential side effects, and effectiveness: yes/no assessed as a reduction of at least 50% of attacks after at least 3 months of treatment compared to the pre-treatment period) along with the characteristics of the headaches (presence of aura, occurrence of other primary headaches, and frequency of headaches experienced in the past three months). Moreover, blood test results and any previous neuroimaging are reviewed to exclude secondary causes of headache and to assess comorbidities relevant to treatment decisions.

Based on all collected data, the neurologist formulates a diagnosis following the International Classification of Headache Disorders (ICHD-III, 2018) [53], distinguishing between migraine (with or without aura), chronic migraine (≥15 headache days/month for >3 months), tension-type headache, medication overuse headache, and other primary or secondary headache disorders. The neurologist also formulates a personalized treatment plan including acute medications, preventive pharmacological therapy (e.g., beta-blockers, antiepileptics, calcitonin gene-related peptide (CGRP) monoclonal antibodies), and non-pharmacological strategies (lifestyle modifications, biofeedback, physical therapy referral). During this phase, participants will receive detailed information about the project, and an informed consent form, along with a data processing form, will be presented for their signature.

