Trophic tones will be assessed with isotonic and isometric evaluations of abdominal muscles, gluteus medius, minimus, maximus, and spinal extensors. Evaluation of spinal curve accentuations, inversions, or extensions, especially dorsal and cervical, will be conducted in the sagittal plane to identify alterations in head posture that may affect MIGs, including specific cervical. The postural examination will conclude with neuromotor tests: Fukuda and Romberg tests (simple, monopodalic, and sensitized) will be used to assess general proprioception and balance [57].

This assessment will be followed by specific tests to evaluate how muscle contracture or weakness, cervical stiffness or instability, and poor posture may influence chronic or episodic MIG, focusing on the neck and cervical-dorsal muscles.

(e) Gnathological assessment will be conducted in accordance with the international diagnostic criteria (DC)/TMD [58]. This involves a thorough medical history of the disorders, followed by an examination of two reference axes. AXIS I focuses on identifying isolated muscle pain, condylar-disk dislocations, arthralgia, or degenerative bone changes within the temporomandibular joints, whereas AXIS II explores the psychological factors that influence the progression of the pathology and chronic pain. Participants will undergo a 4-channel surface electromyography (Teethan) examination [59]. The Baiobit motion sensor will also be used to perform cervical ROM [60,61], balance, and gait tests to identify ascending or descending interference factors in TMD.

After the evaluation, participants will be randomly assigned to two groups: the control group (*n* = 100), comprising people with MIG in standard care; and the intervention group (*n* = 100), comprising people with MIG in standard care plus supervised EXE intervention. Only the second group will attend a supervised, mixed EXE intervention (phase 3).

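### The primary model could gain some precision, at almost no cost, by adding preventive-drug status fixed before randomisation to its single covariate

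*Protocol article*

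**What the plan says.** Section 2.4 of the protocol article sets out the primary analysis as a linear mixed-effects model with the group-by-time term as its fixed effect and "the baseline number of MIG/month value as the covariate". No other covariate is named. Adherence to exercise and to patient education enters only as a process variable.

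Section 2.2.1 describes the enrolment visit. On existing treatment, "we will gather details regarding prophylactic medications", with timing, dosage, side effects and effectiveness. Effectiveness is a yes/no item, "assessed as a reduction of at least 50% of attacks after at least 3 months of treatment". At the same visit, "The neurologist also formulates a personalized treatment plan including acute medications, preventive pharmacological therapy". Headache frequency over the preceding three months is also taken then.

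Section 2.2.2 places allocation after all of this: "After the evaluation, participants will be randomly assigned to two groups". No stratification factor is mentioned.

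Section 2.1 defines the two migraine types by monthly frequency: "chronic (≥15 attacks/month, for at least 3 months) or episodic and high frequency (8–14 attacks/month) MIG".

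**The concern.** Participants are recruited at a first specialist visit, a setting where some of them may plausibly start or change a preventive drug. The outcome is measured at 6 and 12 months, after such a drug has had time to act. If the baseline value comes from the history before the visit, it cannot tell a patient about to start a preventive from one who is not. Variation in the outcome due to those starts then stays in the residual, although the status is known before allocation and could be removed.

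The loss matters more because the design has little slack. As shown below, the stated 100 per group matches the requirement before dropout, not after it.

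**Working it through.** **Inputs from section 2.4.** 5% significance (taken as two-sided), 80% power, 1:1 allocation, a difference of about 2 headache days, a fall of 15–20% from baseline, SD about 50% of the mean, and 30% dropout. A fall of 2 days is 20% of a mean of 10 (SD 5) or 15% of a mean of 13.3 (SD 6.67). The article uses a change from baseline as the between-group difference, and plans in days while the endpoint is a count of migraines. I follow it on both here.

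**The plan's own figure.** n per arm = 2 × (1.96 + 0.842)² × SD² / 2².
- SD 5: 98.1, so 99 per arm, in line with the stated 100. Allowing for 30% dropout, 99 / 0.7 = 142 per arm.
- SD 6.67: 175 per arm before dropout.

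So 100 enrolled per arm leaves about 70 evaluable. Two-sample t power at 70 per arm without any covariate is 65% (SD 5) or 42% (SD 6.67).

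**The planned model.** Baseline adjustment must be included before asking what a further covariate adds. With an assumed baseline–outcome correlation of 0.5, the residual variance is SD² × (1 − 0.5²):
- SD 5: 25 × 0.75 = 18.75 (residual SD 4.33). Standard error of the difference √(18.75 × 2/70) = 0.73, power 77.4%.
- SD 6.67: 44.4 × 0.75 = 33.3 (residual SD 5.77). Standard error 0.98, power 53.0%.

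**Adding preventive status.** Take a binary start, independent of the baseline count, with share p and mean effect g. It accounts for variance g² × p(1 − p), which adjustment removes. Both p = 30–50% and g = 1–4 attacks are assumptions. The calculation is for one follow-up visit.

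| g | Variance removed | Power, SD 5 (from 77.4%) | Power, SD 6.67 (from 53.0%) |
|---|---|---|---|
| 1 | 0.21–0.25 | 77.9–78.0% | 53.3% |
| 2 | 0.84–1.00 | 79.3–79.6% | 54.0–54.2% |
| 3 | 1.89–2.25 | 81.6–82.5% | 55.4–55.9% |
| 4 | 3.36–4.00 | 85.0–86.4% | 57.4–58.3% |

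The share of residual variance removed is about 1–21% with SD 5 and 1–12% with SD 6.67.

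**Chance imbalance.** The between-arm difference in the proportion of starters has SD √(2p(1 − p)/70) = 7.7 to 8.5 percentage points, so a 95% range of ±15 to ±17 points. For g = 2 this moves the estimate by at most ±0.30 to ±0.33. It is not an extra loss. With p = 30%, its variance is 2² × 2 × 0.21/70 = 0.024. The unadjusted squared standard error is 18.75 × 2/70 = 0.536, and 0.536 − 0.024 = 0.512, whose root is 0.715. That is exactly the adjusted standard error for that case.

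**Migraine type.** Type is a cut at 15 on the frequency already in the model. In simulated baseline counts (uniform, skewed, and half in each type), the correlation between count and type was 0.82–0.85. An extra step of 0–3 attacks at the cut gave type a partial R² of 0 to 3.4%. Preventive status with a partial R² of 4.5% (g = 2, p = 30%, SD 5) gained 1.9 points, so type gains less than that even at the extreme.

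**The case against.** The strongest reply is that baseline count is a sound covariate, the model is valid as written, and further covariates may sit in an analysis plan that is not shown. That largely stands: nothing here is wrong or contradictory. But the article does state its primary model and name its covariate, so the suggestion concerns a stated choice. If the full plan already includes preventive status, the point falls.

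Some premises are softer than they look. The article does not fix the window for the baseline value: section 2.2.1 takes a three-month history, while section 2.3.1 has attacks tracked by diary. A diary kept after the visit could already show some drug effect. Nor does the article describe a field that marks a preventive as newly started or changed at enrolment.

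Three stronger readings are tempting but not supported:
- A reader might infer that chance imbalance in drug starts biases the result. Under randomisation it does not, and the model's standard error already covers it.
- A reader might set the 50% reduction against the 15–20% expected from exercise and conclude that drugs will swamp the effect. The 50% is a responder threshold for recording whether a drug worked, not a mean effect among starters. The documents give no mean effect.
- A reader might expect a similar gain from adding migraine type. It largely duplicates the baseline count.

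**Conclusion.** The point holds as an efficiency improvement. One prognostic factor, knowable before randomisation and largely recorded already, is left out of the primary model. The gain runs from under 1 power point (1-attack drug effect) to about 9 points (4 attacks, half the patients starting, SD 5). With SD 6.67 it never exceeds about 5 points. At a 2-attack effect it is 1–2 points in either case. These figures rest on the assumed correlation of 0.5, starter share, drug effects and 70 evaluable per arm. The adjustment does not make good the shortfall in sample size after dropout.

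**What to change.** In section 2.4, add to the primary mixed model a pre-specified fixed covariate for preventive-drug status as fixed before randomisation, with three levels: none, continuing, newly started or changed. State that it is recorded before allocation is revealed. State also that drug starts or changes after randomisation will not be used as covariates, because in this open trial they may depend on allocation. Do not add migraine type in the expectation of a gain.

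The cost is about two degrees of freedom, a sentence or two of analysis text, and one field to complete before allocation. It should be settled before outcome data are seen, so that the choice cannot look data-driven.
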